## Abstract

**Background:**

Despite many efforts, long wait times and overcrowding in emergency departments (EDs) have remained a significant health service issue in Canada. For several years, Canada has had one of the longest wait times among the Organisation for Economic Co-operation and Development countries. From a patient’s perspective, this challenge has been described as “patients wait in pain or discomfort for hours before being seen at EDs.” To overcome the challenge of increased wait times, we developed an innovative ED management platform called *SurgeCon* that was designed based on continuous quality improvement principles to maintain patient flow and mitigate the impact of patient surge on ED efficiency. The SurgeCon quality improvement intervention includes a protocol-driven software platform, restructures ED organization and workflow, and aims to establish a more patient-centric environment. We piloted SurgeCon at an ED in Carbonear, Newfoundland and Labrador, and found that there was a 32% reduction in ED wait times.

**Objective:**

The primary objective of this trial is to determine the effects of SurgeCon on ED performance by assessing its impact on length of stay, the time to a physician’s initial assessment, and the number of patients leaving the ED without being seen by a physician. The secondary objectives of this study are to evaluate SurgeCon’s effects on patient satisfaction and patient-reported experiences with ED wait times and its ability to create better-value care by reducing the per-patient cost of delivering ED services.

**Methods:**

The implementation of the intervention will be assessed using a comparative effectiveness-implementation hybrid design. This type of hybrid design is known to shorten the amount of time associated with transitioning interventions from being the focus of research to being used for practice and health care services. All EDs with 24/7 on-site physician support (category *A* hospitals) will be enrolled in a 31-month, pragmatic, stepped wedge cluster randomized trial. All clusters (hospitals) will start with a baseline period of usual care and will be randomized to determine the order and timing of transitioning to intervention care until all hospitals are using the intervention to manage and operationalize their EDs.

**Results:**

Data collection for this study is continuing. As of February 2022, a total of 570 randomly selected patients have participated in telephone interviews concerning patient-reported experiences and patient satisfaction with ED wait times. The first of the 4 EDs was randomly selected, and it is currently using SurgeCon’s eHealth platform and applying efficiency principles that have been learned through training since September 2021. The second randomly selected site will begin intervention implementation in winter 2022.

**Conclusions:**

By assessing the impact of SurgeCon on ED services, we hope to be able to improve wait times and create better-value ED care in this health care context.

**Trial Registration:**

ClinicalTrials.gov NCT04789902; https://clinicaltrials.gov/ct2/show/NCT04789902

**International Registered Report Identifier (IRRID):**

DERR1-10.2196/30454

## Introduction

### Background

Long wait times and overcrowding are challenging emergency departments (EDs) around the world [1-4]. Several other countries with advanced health care systems cannot keep pace with patient demand. In particular, Canada ranks among countries with the longest wait times compared with those of peer-industrialized countries [5]. The Canadian Institute for Health Information (CIHI) reported an 11% increase in ED wait times from 2015-2016 to 2016-2017 [2]. This translates to long wait times and deters patients from pursuing the necessary care they need and increases the likelihood of patients leaving the ED without being seen (LWBS) by a physician [6,7]. In Newfoundland and Labrador, Canada’s easternmost province, long wait times are plaguing the province much like the rest of Canada [8-10].

The Newfoundland and Labrador provincial government and the province’s 4 regional health authorities (RHAs) have the option of expanding the health care workforce [11,12] at a time of historic fiscal restraint or finding effective interventions to improve the efficiency of their current ED service [13]. Overtime [14-16], expanding the ED [17,18] and redirecting patients to primary care [19,20] have not been shown to be effective. According to an October 2020 report from the CIHI, ED services are making up a larger percentage of total hospital spending with a 4% annual growth rate, which was observed between 2005 and 2019 [21]. The same report states that ED staff are twice as likely to work overtime compared with staff in other departments [21].

We have created a quality improvement intervention called SurgeCon. As a pragmatic ED management platform, SurgeCon includes 3 separate components (described below) that together act to decrease wait times and improve the sustainability of Newfoundland and Labrador’s ED services without significant workforce changes. These interventions include restructuring the ED organization and workflow, fostering a patient-centric environment, and quantifying ED demands and available resources in real time. SurgeCon is designed to enable frontline health care workers to anticipate and mitigate surges in patient volume through a series of proactive steps and decision-making tools. SurgeCon attracted the attention of the Newfoundland and Labrador Eastern Health (EH) RHA after they missed their own ED wait time benchmarks in 2016 [22]. The initial development of the SurgeCon intervention came about after an external review was completed by an independent third party to determine which areas of ED operations could be adjusted to improve wait times and departmental efficiency. The external review was one of many components included in a provincial wait time reduction initiative [23].

We piloted SurgeCon at the ED located in Carbonear, Newfoundland and Labrador, an EH administered hospital, over 45 months from July 1, 2013, to March 31, 2017. Data from the pilot study were analyzed using an interrupted time series analysis to assess its effect on ED performance. The resulting change in indicators was noteworthy, despite a 25.7% increase in patient volume. Over the course of the 45-month pilot study, average time to physician’s initial assessment (PIA) decreased from 104.3 (SD 9.9) minutes to 42.2 (SD 8.1) minutes, length of stay (LOS) in the ED decreased from 199.4 (SD 16.8) minutes to 134.4 (SD 14.5) minutes, and the number of patients LWBS decreased from 12.1% (SD 2.2%) to 4.6% (SD 1.7%). All of these changes were statistically significant. The marked and sustained impact of SurgeCon on ED performance in Carbonear supports the case for its extension to other EDs.

The proposed innovative clinical trial and the implementation of SurgeCon (see the implementation paper) [24] will generate practical information on its effectiveness in a range of urban and rural ED settings and generate data to support its more comprehensive implementation. Given the successful results from the pilot study, and if SurgeCon proves to address ED patient flow issues in this study, the rest of Canada and other countries could significantly benefit from its implementation.

Given the scope of the SurgeCon research program, a separate protocol related to evaluating the intervention’s implementation was published in a separate article [24]. This research protocol focuses on the innovative clinical trial stepped wedge cluster randomized trial (SW-CRT) design used to assess the effectiveness of the intervention. In this protocol paper, we will provide a brief description of the intervention and associated research activities that will be carried out at each of the 4 selected ED sites.

### Study Aim and Objectives

In this study, we present the protocol for a 31-month SW-CRT trial. Our aim is to evaluate the performance of the SurgeCon platform in improving important patient and service process outcomes in EDs in an RHA in Newfoundland and Labrador and develop strategies to promote its scalability, sustainability, and successful implementation across the Canadian health system. The primary objective of the trial is to evaluate the effects of SurgeCon on ED performance by assessing its impact on LOS, PIA, and LWBS. The secondary objective of the trial is to assess the intervention’s impact on patient satisfaction and patient-reported experience with ED wait times and its ability to create better-value ED services by reducing ED costs.

## Methods

### Ethics Approval

This study has been approved by the Newfoundland Labrador Health Research Ethics Board with researcher portal file 20201482.

### Study Setting

Newfoundland and Labrador’s health care system is delivered through four RHAs: EH, Central Health, Western Health, and Labrador-Grenfell Health. The eastern RHA will be participating in this research initiative as a collaborative research partner and will be the only RHA participating in the study. The other 3 health authorities will act as knowledge users and will not be included in the SurgeCon trial. However, the research team will provide interim reports to the other health authorities to allow them to monitor and learn from research findings over the course of the study period to guide future implementation in their own centers.

This is a multisite study, including 2 urban and 2 rural EDs with 24/7 on-site physician support in the EH region of Newfoundland (Figure 1). The remaining 2 EDs with 24/7 on-site physician support within the study area that are not receiving the intervention are a pediatric ED, which operates differently and has wait times that differ greatly from adult or general ED, and the Carbonear General Hospital, which was chosen for the pilot study. The 4 sites receiving the intervention include 2 urban sites (Health Sciences Centre and St. Clare’s Mercy Hospital) and 2 rural sites (Dr. G.B. Cross Memorial Hospital and Burin Peninsula Health Care Centre).

**Figure 1 figure1:**
[figure not shown]
Emergency department (ED) locations in 4 regional health authorities of Newfoundland and Labrador (NL). iCT: innovative clinical trial.

### Study Population

All individuals who visited any of the 4 selected EDs during the study period will be included in the collection of deidentified health administrative data. We will also collect and monitor ED-level key performance indicator (KPI) data such as LOS, PIA, and LWBS because they are impacted by patient volume. Patients who receive care at these EDs will be randomly selected for subsequent follow-up after they are discharged to collect information related to their experience in the ED and to determine their level of satisfaction with the care that they received.

### Site Randomization

As we will be evaluating the effectiveness of SurgeCon using an SW-CRT, the 4 different hospitals will be randomized, with 1 ED site starting at the first sequence. The next site will start 6 months later in the second sequence and will continue until all EDs are allocated to sequences. A simple random sample will be performed by the study statistician, who will generate a randomization list using statistical software that will determine the order of intervention implementation. The researchers and participants will not be blinded to whether they are in the intervention or the control cohort.

### Patient Randomization

To assess patient-reported experiences and satisfaction, discharged patients who are subsequently contacted to complete satisfaction and patient experience surveys will be randomly selected using a random time and date generator program.

### Study Outcomes

The SurgeCon study aims to measure both ED KPIs (LOS, PIA, and LWBS) and patient perceptions and satisfaction related to the care they received in the ED. Patient health outcomes, use of health care resources, and overall cost will also be assessed based on a patient’s arrival time. We will also collect information on the potential adverse effects of the intervention such as 24-hour readmission and mortality. These data will help examine trends in mortality and readmissions before and after intervention implementation.

The study uses a comparative effectiveness-implementation hybrid design and includes outcomes for effectiveness and implementation. Two measurement levels will be considered for the study, ED- or service-level and patient-level outcomes will be used to determine the effectiveness of SurgeCon. To guide our choice of outcomes and to determine how best to evaluate the intervention’s implementation, we applied a combination of 2 frameworks, that is, RE-AIM (reach, effectiveness, adoption, implementation, and maintenance) and Consolidated Framework for Implementation Research [25,26]. To guide our implementation strategy, we will collect data related to organizational climate, fidelity of staff training, fidelity of intervention delivery, implementation cost, barriers and enablers to adoption, implementation, institutionalization, intervention acceptability, intervention appropriateness, feasibility of maintaining SurgeCon, sustainability of SurgeCon, and scalability of the SurgeCon intervention. Detailed information on implementation assessment and outcomes is available via our other work [24].

### Study Design

The SW-CRT design is a novel, robust, and flexible 1-way crossover cluster randomized trial design increasingly being used in trial arms with varying time delays in which all clusters start from the control condition to the active intervention condition state. In particular, this longitudinal stepped wedge study design includes a repeated cross-sectional design, as illustrated in Figure 2, where each hospital will eventually receive the intervention. All participating sites will begin the trial in a control condition where they will continue to use a usual care model or the model of care provided before the beginning of the trial. Each site will switch from providing usual care to providing care using the intervention that will take place at predetermined time periods during the study. At the end of the trial experiment, each of the sites will have implemented all of the intervention’s components. The stepped wedge randomized trial design used in this study is normally carried out at the cluster level rather than at the individual level. Therefore, a clustered randomized stepped wedge design will be the focus of this protocol.

**Figure 2 figure2:**
[figure not shown]
Schematic representation of a SW-CRT with 4 steps for a 31-month study period. 
SW-CRT: stepped wedge cluster randomized trial.

The advantages of the SW-CRT include logistical flexibilities, efficiencies in terms of power, and sample size compared with traditional (clustered) parallel-group designs. Furthermore, the ethical advantages in longitudinal and open cohort studies have also been recognized [27-29]. A simple random sampling technique will be used to determine the order of intervention implementation across the 4 selected sites. The assignment of 1 cluster per sequence will maximize statistical power. The study period can be subdivided by four 6-month steps. Each step starts with the implementation of the intervention at one of the 4 selected sites. Observations are collected repeatedly from each cluster in multiple periods. The key parameters such as the number of clusters or clusters per sequence, steps, and measurement periods (both control and intervention conditions), intracluster correlation coefficient (ICC), and effect size are required for sample size calculation for the SW-CRT design.

The total study period available for the intervention to remain active is 31 months, and it is expected that at least one month will be needed for training and implementation at each ED site. A 1-month intervention adoption period was considered to be sufficient for the intervention to be fully operationalized for a single cluster. During the first 6 months of the baseline period, all patients who visit any of the 4 hospitals will receive usual care. After the baseline period, a randomly allocated hospital will begin SurgeCon intervention implementation every 6 months and will continue to use the intervention for operations and management until the end of the study. Staff at each of the randomly selected hospitals will undergo training, establish processes and guidelines that are consistent with efficiency principles covered during training, and begin routine data entry. During the last 6 months of the study period, all 4 hospitals will be operating using the SurgeCon ED management platform exclusively. We will be monitoring the characteristics of each hospital and the composition of their associated frontline teams to determine if significant changes have occurred since the control period and whether an adjustment to our analysis plan is required.

### Sample Size

On the basis of the results of a pilot study conducted at a rural ED site in EH’s jurisdiction, we established a common framework for optimal sample size calculations when the number of clusters available for randomization is limited to 4 sites for the SW-CRT design. We chose 1 cluster, which will cross over to an intervention state at a randomly assigned step. To keep things relatively simple, we assume that an equal number of observations is sampled in each cross section of each cluster. Alternatively, we expect an equal amount of observations per period per cluster. Results from our pilot study show a 15% to 30% decrease in the LOS or wait times between 6 and 30 months after SurgeCon implementation [30-32]. This trial is powered to detect a 15% change in LOS at 5% of type I error and 80% power with an ICC [33] of 0.1 for repeated measures (6 measures per step). A 10% reduction in ED wait time in the study sites could result in 10-minute reduction in LOS. To detect this change, a minimum sample size of N=20,280 (169/month/hospital for 30 months and 4 hospitals) is required. To be able to conduct age, sex, and patient acuity subgroup analyses for all ED visits across the 4 intervention sites, we will include all ED visits for this portion of the analysis as there is a low cost associated with extracting data from existing ED repositories, which routinely capture patient record-level information. For patient satisfaction, the study is powered to detect a 30% change in patient-reported experience measures or patient satisfaction [34-37] at a 5% of type I error and 80% power with an ICC of 0.1. Therefore, a sample size of 1320 (11/month/hospital for 30 months and 4 hospitals) would be sufficient for this study. Considering a 50% response rate, we will conduct 25 surveys per month per hospital. In particular, we demonstrated the required sample size and power calculation procedure with illustration for different combinations of the ICC to detect the standard effect size. For this illustrative purpose, we consider a clinical trial powered to detect a 10% to 30% reduction in wait times on a continuous scale at the 4 different EDs with 5% of type I error rate and 80% power.

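### The Sample Size section gives two different LOS targets for one sample size; N=20,280 can be the 80%-power minimum for only one of them

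*Protocol article*

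**What the plan says.** Everything at issue is in the Sample Size section of the protocol article, apart from the pilot figures under Background.

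- Power claim: "This trial is powered to detect a 15% change in LOS at 5% of type I error and 80% power". The assumed ICC is 0.1, and each step has six repeated measures.
- The next sentence brings in a different quantity: "A 10% reduction in ED wait time in the study sites could result in 10-minute reduction in LOS".
- The sample size follows directly: "To detect this change, a minimum sample size of N=20,280 (169/month/hospital for 30 months and 4 hospitals) is required".
- Later, described as illustrative: "we consider a clinical trial powered to detect a 10% to 30% reduction in wait times on a continuous scale".
- The section says the calculation rests on the pilot. In the pilot, "length of stay (LOS) in the ED decreased from 199.4 (SD 16.8) minutes to 134.4 (SD 14.5) minutes", and time to physician's initial assessment (PIA) "decreased from 104.3 (SD 9.9) minutes to 42.2 (SD 8.1) minutes".
- The section also says that all ED visits will be analysed, to allow subgroup analyses.

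The article gives no mean LOS for the four study sites and no patient-level SD of LOS.

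**The concern.** LOS is one of the three primary outcomes and the one on which the trial is sized. Two consecutive statements attach 80% power and a minimum N to it, but they name different effects. The explicit power claim is for 15% of LOS. The sample size is tied to the change just mentioned, which is 10 minutes. If the two are not the same effect, one of them is wrong as a sizing statement: either 80% is not the power for 15%, or 20,280 is not the minimum for 10 minutes. A reader then does not know which LOS effect the design was built to detect.

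**Working it through.** **1. The plan's own product.** 169 × 30 × 4 = 20,280. This is correct. The 169 itself cannot be derived from the article, because the patient-level SD is not stated.

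**2. The two targets on one scale** (baseline LOS 199.4 min, pilot, Background).

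- 15% of LOS: 0.15 × 199.4 = 29.9 min.
- 10 min as a share of LOS: 10 / 199.4 = 5.0%.
- Ratio of effects: 29.91 / 10 = 2.991.
- The targets coincide when 0.15 × L = 10, so L = 66.7 min. The pilot's post-intervention mean was 134.4 min, about twice that.

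**3. Ratio of required sample sizes.** With required N proportional to 1/effect², the ratio is (0.15 × L / 10)²:

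| Baseline LOS (min) | 15% (min) | Ratio of N |
|---|---|---|
| 100 (assumed) | 15.0 | 2.25 |
| 150 (assumed) | 22.5 | 5.1 |
| 199.4 (pilot) | 29.9 | 8.9 |
| 300 (assumed) | 45.0 | 20 |

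The SD cancels, so the ratio does not depend on it.

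**4. What 169 per month per hospital can detect.** The article does not name its sample size formula. I used the constant-ICC stepped-wedge (Hussey–Hughes) variance with I = 4 hospitals, T = 30 months, one hospital crossing every 6 months after a 6-month baseline, ICC 0.1, total SD = 1 and two-sided 5%:

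Var = I·s²(s² + T·τ²) / [(I·U − W)s² + (U² + I·T·U − T·W − I·V)τ²]

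- τ² = 0.1; s² = 0.9 / 169 = 0.005325.
- U = 24 + 18 + 12 + 6 = 60.
- W = 6 × (0 + 1 + 4 + 9 + 16) = 180.
- V = 24² + 18² + 12² + 6² = 1,080.
- Numerator: 4 × 0.005325 × 3.005325 = 0.06402.
- Denominator: 60 × 0.005325 + 1,080 × 0.1 = 108.32.
- Var = 0.000591; SE = 0.0243 SD.
- Detectable effect at 80% power: (1.960 + 0.842) × 0.0243 = 0.068 SD.

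Treating the trial as five 6-month periods of 1,014 visits gives the same 0.068 SD.

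**5. The SD each target would need for N=20,280 to give 80% power.**

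- 10 min: 10 / 0.0681 = 147 min.
- 29.9 min: 29.91 / 0.0681 = 439 min.

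Both SDs are back-solved, so neither is evidence about which target was used.

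**6. Consequence of each reading.**

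- N sized for 10 min (SD 147): power for 29.9 min exceeds 99.9%, and the minimum for 29.9 min would be 19 per month per hospital, or 19 × 120 = 2,280 visits.
- N sized for 29.9 min (SD 439): power for 10 min is Φ(2.802 / 2.991 − 1.960) = Φ(−1.023) = 15%, and the minimum for 10 min would be 1,514 per month per hospital, or 1,514 × 120 = 181,680 visits.

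**7. Power at N=20,280 over a range of assumed SDs.**

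| Patient-level SD (min) | Power, 10 min | Power, 29.9 min |
|---|---|---|
| 100 | 98% | >99.9% |
| 150 | 78% | >99.9% |
| 200 | 54% | >99.9% |
| 300 | 28% | 98% |
| 400 | 18% | 87% |

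The SDs of 16.8 and 14.5 min printed with the pilot LOS appear to be SDs of period averages. Used as patient-level SDs they give power near 100% for both targets and do not lead to 169.

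**The case against.** The strongest reply is that the statements do not strictly conflict. If N was set for 10 minutes, which is the nearest antecedent, the trial is also powered for 15%, with power to spare. That stands: the targets are not mutually exclusive, and on this reading the 15% sentence is true in the loose sense of at least 80%. As a sizing statement it still fails, because the power is not 80% and 20,280 is not the minimum for 15%.

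Three further inferences are tempting but not supported.

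- *That a percentage of wait time was wrongly carried over to LOS.* The text goes from a percentage of wait time to minutes of LOS. Ten percent of the pilot PIA is 0.10 × 104.3 = 10.4 min, and if waiting is part of LOS, about 10 minutes off the wait is about 10 minutes off LOS. That step is coherent.
- *That the back-solved SD of 147 min confirms the 10-minute reading.* It was obtained from 169 and 10 minutes, so it must return them.
- *That a null result could not be interpreted.* What a null result excludes depends on the confidence interval, and the Analyses section commits to reporting each effect with its precision.

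It may also be said that a journal article can leave the SD and baseline to the full protocol. That is fair, and their absence is not the charge. The charge is that two printed statements give one N two targets. The illustrative 10% to 30% range does not settle this, because it concerns wait times and adds further targets.

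**Conclusion.** The section is wrong as written. N=20,280 can be the 80%-power minimum for a 15% change in LOS or for a 10-minute change, but not for both. On the pilot baseline the effects differ 3-fold and the required N about 9-fold. Only a mean LOS of 66.7 min would reconcile them.

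The 9-fold figure rests on the pilot baseline and on a variance that falls in proportion to 1/n, which holds almost exactly in the model used here. The SDs of 147 and 439 min also depend on that model, on ICC 0.1 and on a two-sided test. The article does not state sidedness; a one-sided 5% test raises the implied SDs to about 165 and 495 min and leaves their ratio unchanged.

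A reader might infer that the trial is underpowered. The document does not support that: low power for 10 minutes arises only if N was sized for 15%, nothing printed shows that it was, and the analysis will use all ED visits with 20,280 as a floor. Severity is moderate.

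**What to change.** In the Sample Size section, state the one LOS target to which N=20,280 at 80% power belongs, in minutes and as a percent of a named baseline LOS. Then either restate the other target as a secondary figure with its own power or remove it. If N belongs to 10 minutes, the 15% sentence can stay as a secondary statement with its higher power. If N belongs to 15%, the words linking N to the 10-minute change must go. Giving the patient-level SD and the sidedness used would let a reader reproduce the 169.

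The cost is a few sentences of text. Enrolment, randomisation and analysis do not change, because all ED visits are included.
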